| STATISTICAL ANALYSIS | **Descriptive statistics**  **Comparison of groups**  The trial being a non-inferiority trial, the main analysis will be a per-protocol analysis to be conservative by increasing the contrast between the groups.  Main objective  The active spa therapy will not be considered inferior to the standard spa therapy if the lower bound of the confidence interval at 90% of the difference between the 2 groups (active spa therapy minus standard spa therapy) for the main outcome criterion (percentage of respondents according to the composite criterion) is not less than 15%. After verification of the randomization that could be unbalanced due to the Zelen randomization mode, the final analysis will be adjusted if necessary on the variables that differ between the 2 groups.  Secondary objectives  - The same analyses will be repeated for the MCII composite criterion, pain and function at 3 months, and PASS criteria.  - To determine the predictive factors of spa therapy response, a bivariate analysis will be performed using chi-square tests (or Fisher exact tests depending on the number) for discrete variables and Student t-tests, ANOVA or Wilcoxon tests for quantitative variables. The parameters significant on bivariate analyses (at the conservative threshold of p=0.1) will then be introduced into a stepwise multiple logistic regression.  P<0.05 will be considered statistically significant.  The statistical analysis will be carried out by the Centre for Clinical Epidemiology by using SAS v9.2 (SAS Inc., Cary, NC). |
| EXPECTED FALLBACK | To be able to offer different types of spa therapy in order to adapt to patients' preferences.  Propose a spa therapy that can be performed externally near the patient’s home.  Offer a less tiring cure.  Obtaining thermal approval for the Nancy Thermal site. |

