**3. RESEARCH OBJECTIVES**

The purpose of this study is to compare the 6-month efficacy of two types of spa therapy: "standard spa therapy" (spa therapy delivered 6 days out of 7 for 3 consecutive weeks) and "active spa therapy” successively combining iterative spa sessions (3 sessions per week for 3 weeks) then specific re-education (3 sessions per week for 3 weeks).

The main objective of the study is to compare the proportion of patients with a composite response criterion combining the MCII for pain and/or functional ability and the absence of knee surgery on the targeted knee at 6 months, according to two types of spa therapy ("standard spa therapy" and "active spa therapy") in symptomatic knee OA.

The secondary objectives are as follows:

- To compare the effectiveness of the two types of spa therapy on pain and function at the end of the spa therapy and at 3 months

- To determine the evolution of quality of life scores (OAKHQOL, SF-36), of fatigue, patient satisfaction, medication use and care, as well as the use of surgery in both types of spa therapy

- To describe the effectiveness of standard spa therapy in Nancy Thermal on pain and functional abilities by an analysis of the before and after effect

- To describe the postural anomalies encountered with knee OA by a posturographic study and to evaluate the evolution of these anomalies according to the type of spa therapy and over time.

- To study the predictive factors of response to spa therapy (socio-demographic data, clinical, radiographic, ultrasonography and posturographic) at 3 and 6 months.

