- Demographics: age, sex, level of education, current or former professional activity, place of residence (size of the municipality)
- Medical history and co-morbidities (Groll functional index)
- Medication
- History of knee OA: initial trauma (rupture of the cruciate ligament knee or lower limb fracture), presence of the symptoms before the current painful episode, duration of the current episode, previous drug treatments (corticosteroid injections, viscosupplementation, symptomatic treatments [analgesics, NSAIDs, symptomatic slow-acting drugs for osteoarthritis" (SySADOA)]) and non-drugs (surgery [osteotomy, arthroscopy, meniscectomy], spa treatment, rehabilitation, other etc.)
- Clinical data: weight, height, static disorders, length inequality of the lower limbs.
- X-rays of < 6 months with weight-bearing, full extended-knee X-ray and Schuss. The radiographs will be digitized for a centralized reading and will be used to confirm the diagnosis of femorotibial OA (Kellgren and Lawrence stage ≥2).
- Posturography examination
- Ultrasound examination

During other visits

Clinical and perceived health data will be collected before the cure (V0), at 3 weeks (V1: end of the standard spa therapy or change of type of care for active spa therapy), at 6 weeks (V2: end of active spa therapy), at 3 months (V3: M3) and 6 months (V4: M6) and will include the following examinations: clinical exam (effusion, joint amplitudes), VAS-pain, VAS-fatigue, WOMAC, OAKHQOL, SF-36, satisfaction, drug consumption, surgery, side effects, posturography examination, 6-minute walk. The number of treatments actually performed by the patients will also be collected.

The assessor will be blinded to the treatment group at 3 and 6 months.

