This examination is carried out by the investigating physician. It allows for classifying knee OA in congestive or non-congestive forms at inclusion. This non-radiant and non-traumatic exam will help to appreciate the importance of joint effusion and synovitis and to objectify the presence of a popliteal cyst by using a score validated for the first time in this type of population [6]. Joint effusion and synovitis will be evaluated on 3 regions of interest: median, medial and lateral quadricipital ramps. The vascular activity of synovitis will be explored in power Doppler mode.

The presence of a popliteal cyst will be sought in the ventral decubitus.

The effusion varies from 0 to 9 and will be considered positive at ≥ 1. The synovitis score ranges from 0 to 15 and will be considered positive at ≥ 1.

The presence of a popliteal cyst will be rated binary: present or absent [6].

Posturography

The posturography examination will be the responsibility of [name] and his team. The examination will be conducted by using a movable platform in a room with sound insulation to avoid interference. The posturography examination is performed without and then with the use of glasses of virtual reality that will distort vision (eyes open/closed/vision distorted) in static and then dynamic situations (foam or swashplate).

At least 6 data points will be acquired. The examination will assess the components proprioceptive, visual and vestibular that come into play in the individual's postural balance [4]. Proprioceptive control appears to fail during knee OA [11], but this study will make it possible to measure the impact of the classical and active spa therapy by measuring the change in length travelled and/or the area covered by the foot pressure centre after the suppression or disruption of sensory inputs and/or somesthesics during treatment and follow-up[ 4]. A recent review showed that active rehabilitation improves control proprioceptive [59].

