**Comparison of groups**

The trial being a non-inferiority trial, the main analysis will be per protocol to be conservative by increasing the contrast between the groups.

Main objective

The active spa therapy will not be considered inferior to the standard spa therapy if the lower bound of the confidence interval at 90% of the difference between the 2 groups (active spa therapy minus standard spa therapy) for the main outcome criterion (percentage of respondents according to the composite criterion) is not less than 15%[1]. After verification of the randomization that could be unbalanced owing to the Zelen randomization mode, the final analysis will be adjusted if necessary on the variables that differ between the 2 groups.

Secondary objectives

- The same analyses will be repeated for the MCII composite criterion, pain and function at 3 months and for PASS criteria.

- To determine the predictive factors of spa therapy response, a bivariate analysis will be performed using chi-square tests (or Fisher exact tests depending on the number) for discrete variables, and Student t-tests, ANOVA or Wilcoxon tests for quantitative variables. The parameters significant on bivariate analyses (at the conservative threshold of p=0.1) will then be introduced into a stepwise multiple logistic regression.

A value of p<0.05 will be considered statistically significant.

The statistical analysis will be carried out by the Centre for Clinical Epidemiology by using SAS v9.2 (SAS Inc., Cary, NC).

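### Predictors of response are chosen by a p<0.1 screen and then stepwise regression, with no shrinkage or validation, so results reported after selection will be over-optimistic

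*Protocol*

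**What the plan says.** Section 3 of the protocol lists as its last secondary objective: "To study the predictive factors of response to spa therapy (socio-demographic data, clinical, radiographic, ultrasonography and posturographic) at 3 and 6 months". Five domains are named, without a list of variables. The summary also gives the absence of any study of such predictors as a gap in the evidence.

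Section 9, under the comparison of groups, fixes the method. Each candidate is tested on its own against response (chi-square or Fisher tests; t-tests, ANOVA or Wilcoxon tests). Then: "The parameters significant on bivariate analyses (at the conservative threshold of p=0.1) will then be introduced into a stepwise multiple logistic regression". The statistical row of the summary repeats this. Section 9 adds a general statement: "A value of p<0.05 will be considered statistically significant". It gives no entry or stay level for the stepwise step, and it mentions no shrinkage, internal validation or multiplicity control for this search.

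**The concern.** Screening one variable at a time and then selecting stepwise uses the same data to choose the model and to judge it. The tests and intervals printed for the final model treat it as if it had been fixed in advance. Retained coefficients tend to be too large, the apparent discrimination is too high, and a factor that matters only jointly with others can be lost at the screen.

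The threshold described as "at the conservative threshold of p=0.1" passes about one null variable in ten, so it gives no protection against false predictors beyond that of the later step. At stake is a named objective: the trial could report noise variables as predictors of who benefits from spa therapy, with a model that would not perform as well in new patients.

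**Working it through.** **Inputs from the protocol.** Evaluable patients: 135 per group, so 270. Responders: 50% at 6 months, 60% at 3 months (the planning rates for standard spa therapy, applied here to both arms). Screen: p<0.1. Response is studied at two time points.

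**Assumptions.** The number of candidates K is not stated, so K runs from 10 to 40. The stepwise level is taken as 0.05, from the general significance statement. No candidate has a true effect.

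**The plan's own sample size.** For non-inferiority with 50% in both groups, margin 15 points, one-sided 5% and 80% power: n = (1.645 + 0.842)² × 2 × 0.5 × 0.5 / 0.15² = 6.18 × 0.5 / 0.0225 ≈ 138 per group. The protocol states 135, about 2% lower. With 5% loss, 270 × 1.05 = 283.5, which gives the stated 284. Using 270 for the predictor analysis is therefore fair.

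**How many candidates.** Counting baseline items in section 4.2 (inclusion visit) and section 4.8 (assessment tools):
- demographics, 5: "Demographics: age, sex, level of education, current or former professional activity, place of residence (size of the municipality"
- comorbidity and medication, 2
- osteoarthritis history and previous treatments, about 11
- weight, height, static disorders and leg length, 4
- Kellgren and Lawrence stage, 1
- ultrasound, 4
- posturography, at least 6: "At least 6 data points will be acquired"

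Sum: 5 + 2 + 11 + 4 + 1 + 4 + 6 = 33, before further examination items, the walking test, pain VAS and WOMAC. These are items collected; the protocol does not say that all of them are candidates.

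**False predictors.** On average 0.1 × K null variables pass the screen. A variable with p<0.05 on its own always passes p<0.1 and can enter at the first stepwise step, so the chance of at least one false predictor is close to 1 − 0.95^K. Simulations of the whole procedure (270 patients, 50% responders, independent null candidates) agree:

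| K | Mean passing screen | 1 − 0.95^K | Simulated, at least one kept |
|---|---|---|---|
| 10 | 1 | 40% | 38–43% |
| 13 | 1.3 | 49% | 47–49% |
| 20 | 2 | 64% | 63–64% |
| 30 | 3 | 79% | 76–78% |
| 40 | 4 | 87% | 86–89% |

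The ranges span separate simulations with different variable mixes and stepwise variants. With candidates in blocks of five correlated at 0.3, the figures are 50%, 60% and 78% for K = 15, 20 and 30. At correlation 0.6 they are 43%, 54% and 68%.

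These rates are per time point. If the 3- and 6-month searches were independent, the chance for K = 10 would be 1 − 0.95^20 = 64%, and for K = 30 it would be 1 − 0.95^60 = 95%. Both are upper bounds, because the two outcomes are correlated.

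**Discrimination.** Among trials that keep a predictor, mean apparent AUC is 0.598, 0.609 and 0.617 for K = 20, 30 and 40. Over all trials, those with an empty model count as 0.50: for K = 20, 0.63 × 0.598 + 0.37 × 0.50 = 0.56. The range for K = 20 to 40 is about 0.56–0.61. The truth is 0.50.

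**Does dropping selection alone cure it?** No. A full model with 13 null parameters in 270 patients shows at least one p<0.05 in 51–53% of trials (1 − 0.95^13 = 49%), with apparent AUC about 0.62.

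**The case against.** The strongest reply is that the alarming percentages depend on an input the protocol does not give. A reader might infer that the procedure yields false predictors in most trials. That fails below about 14 independent candidates, where 1 − 0.95^K first exceeds 50% (51% at 14), and at K = 15 with strong correlation (43%). The candidate list may properly stand in an analysis plan that is not at hand. This objection stands, which is why the result is given as a range.

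Other points also stand in part:
- The calculations assume that nothing predicts response. Response is an absolute improvement from baseline, so baseline severity may well be related to it. It does not follow that the trial will very probably publish noise. Over-optimism after selection remains when some predictors are real.
- The 0.05 stepwise level is inferred. A laxer level would raise the rates.
- The multiplicity comes mainly from testing many candidates uncorrected, as the 13-parameter result shows, and not from stepwise selection as such.
- *Conservative* can mean reluctant to discard a variable, which 0.1 is. A reader might call the word an error; it is at most ambiguous.
- Nothing keeps treatment arm in the model, and with equal response rates it would pass the screen about one time in ten. Its inclusion could still be settled in the analysis plan. No arm interaction is planned, but the protocol asks who responds to spa therapy, not which therapy suits whom.

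The objective is exploratory and drives no sample size. None of this removes the core point: the protocol itself fixes the selection method.

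**Conclusion.** The point holds as a minor but worthwhile methods improvement. The stated screen and stepwise procedure gives over-optimistic p-values, intervals and discrimination. Under the assumptions above, the chance of at least one false predictor per time point runs from about 40% with 10 candidates to 86–89% with 40. For roughly the 33 items listed, if all were used, it would lie near the 30-candidate figures: 76–78% if independent, 68% with strong correlation. The documents do not support an unconditional claim about most trials, nor an AUC of 0.60–0.62 for every trial, since that figure applies only where a predictor was kept. The non-inferiority conclusion is untouched.

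**What to change.** Replace the screen and stepwise steps in section 9 and in the summary with the following:
- A short candidate list fixed before data lock. At 10 events per parameter, 6 months allows 270 × 0.5 / 10 = 13.5, so about 13. At 3 months, with 60% responders, the smaller class is 270 × 0.4 = 108, so about 10–11.
- Treatment arm included in the model.
- One full logistic model per time point without p-value selection, or a penalised one, which is the better choice if more candidates are kept.
- Shrunken coefficients and bootstrap optimism-corrected discrimination.
- Results labelled exploratory. This is needed because uncorrected tests in a full 13-parameter model still give a false positive in about half of null trials.
- The word *conservative* removed or explained.

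The cost is protocol and analysis-plan wording and some bootstrap programming, with no extra patients, visits or data. The downside is that fewer candidates can be examined.

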**10. RIGHT OF ACCESS TO SOURCE DATA AND DOCUMENTS**

All data and information concerning the patient will remain strictly confidential. Persons with direct access in accordance with the laws and regulations in force, in particular Articles L.1121-3 and R.5121-13 of the Public Health Code (e.g., the investigators, quality control persons, monitors, clinical research assistants, auditors and others called upon to collaborate in the trial) will take all necessary precautions to ensure the confidentiality of information relating to experimental treatment, testing, and those who lend themselves to it, and in particular with regard to their identity and the results obtained. The data collected by these persons during quality controls or audits are then made anonymous.

**11. QUALITY CONTROL AND ASSURANCE**

**11.1 Data quality control**

A Clinical Research Assistant mandated by the Nancy DRI will regularly perform monitoring visits in the investigation centre. On this occasion, this person should have access to the observation books, the medical records and all study documents. This person will check adherence to the protocol as well as the compliance with document sources and data consistency.

**11.2 Monitoring of the centres**

Monitoring in the investigation centre will be regular according to the rate of inclusions and a monitoring plan established by the proponent.

**12. ETHICAL AND REGULATORY ASPECTS**

**12.1 INFORMATION DOCUMENT AND INFORMED CONSENT**

Patients will be able to participate in this study only if they have given their written consent.

Information

Beforehand, they will have received oral and written information from the physician investigator on the purpose of this study, the duration of their participation, the procedures, the benefits, the foreseeable risks, the confidentiality of the data, insurance coverage, coverage of costs related to the trial. All this information will be summarized in an information document given to every patient.

Informed consent

The consent form will be signed in duplicate by the participant and the physician investigator. This document will be given to the patient. The investigator should keep the second copy for a minimum of 15 years.

**12.2 DATA CONFIDENTIALITY**

All data collected will be treated anonymously and covered. by medical confidentiality.

The investigator will ensure that patient confidentiality is maintained. In observation notebooks, patients will be identified by the first initial of the name, the first initial of the first name and the inclusion number.

**12.3 LAWS AND BPC**

The investigators undertake to ensure that this study is carried out in accordance with law no. 2004-806 of August 9, 2004, as well as in accordance with Good Clinical Practices (I.C.H. version 4 of May 1, 1996 and decision of November 24, 2006) and the Declaration of Helsinki (Ethical Principles for Medical Research on Subjects Seoul 2008). To do this, a study contract will be dated and signed between the principal investigators from each participating centre and the sponsor.

**12.4 SUBMISSION OF THE PROTOCOL TO THE CPP AND THE COMPETENT AUTHORITY**

The study sponsor will submit this protocol to CPP EST III, in accordance with the legislation in force of the Public Health Code. The sponsor will request also the authorization of the study to the AFSSAPS before the start of the project.

**12.5 PROTOCOL MODIFICATION**

There will be no change to this protocol without the agreement of the sponsor. The proponent will qualify this change as substantial or not. Any substantial modification must be submitted to the CPP and/or AFSSAPS before its implementation.

**12.6 COMPUTERIZATION OF DATA**

In accordance with the Data Protection Act, the files and freedoms in force, the patient has a right of access, communication, opposition and rectification of personal information, which is provided upon written request to the coordinating investigator.

This research is part of the "Reference Methodology" (MR-001) pursuant to the provisions of article 54 paragraph 5 of the law of January 6, 1978 modified relating to data processing, files and freedoms. This change has been approved by decision of January 5, 2006. NANCY University Hospital signed a commitment to comply with this "Reference Methodology".

**12.7 CURRICULUM VITAE AND SIGNATURE OF THE PROTOCOL**

Before starting the study, the coordinating investigator will provide representatives of the sponsor a copy of his personal CV dated and signed as well as those of the associate investigators.

**12.8 PROMOTION**

The promotion of this trial is ensured by the NANCY University Hospital.

**12.9 STUDY REPORT AND PUBLICATIONS**

The final report of the research will be written by the coordinator and the person responsible for data analysis. This report will be submitted to each of the investigators for their opinion. Once a consensus is reached, the final version must be endorsed by the signature of each of the investigators and sent to the sponsor as soon as possible after the effective end of the search.

Nancy University Hospital is the owner of the data and use or transmission to a third party may not be carried out without its prior consent. NANCY University Hospital must be mentioned as the biomedical research sponsor.

**12.10 FILING AND ARCHIVING**

Research documents falling within the scope of the Research Act biomedical records must be archived by all parties for 15 years after the end of the research. This indexed archiving must include all documents related to the research.

**13. FINANCING**

Budget

This part takes into account the additional costs incurred by the CHU in the service of Rheumatology and CIC-EC INSERM, for the Training Institute in Massokinesitherapy, and for the Department of Physical Medicine and Rehabilitation

Rheumatology Department

Missions: development of the research program, communication, recruitment, data collection (inclusion visit), interpretation of data.

Project preparation: organization of scientific meetings, drafting of the protocol and CRF, coordination with partners: CUGN, CIC EC INSERM, Physical Medicine and Rehabilitation, sponsor; study planning;

Data collection: patient inclusion data

Analysis and interpretation: interpretation, writing report for thermal approval and scientific article

Estimated budget Rheumatology (euros)

|  | Year **2011** | Year **2012** | Year **2013** | **Total** |
| --- | --- | --- | --- | --- |
| Preparation of the draft of the research - Writing of the protocol - Writing a report | 2500 |  | 2500 |  |
| Investigating physician: 98 euros per patient (400 patients examined) |  | 39 200 |  |  |
| Digitized radiographs  19.95 euros per patient (n=400) |  | 7 980 |  |  |
| Computer equipment: Laptop computer, external hard disk backup and camera | 2500 |  |  |  |
| Total | 5000 | 39200 | 2500 | 46700 |

Thermal physician(s):

Missions:

Follow-up of patients during spa therapy,

Adverse reaction reporting

Data collection and evaluation at V0 and V1

Estimated budget: estimated budget 1.5 full-time equivalents March 2012 to December

2012: 100,000 euros

CIC-EC INSERM

Missions: Management of the research project - collection, analysis and interpretation of the data

Project preparation: regulatory dossiers: CPP, AFSSAPS;

Collaboration with the promoter; coordination with partners: CUGN, Rheumatology, rehabilitation; definition and traceability of the patient circuit; coordination meetings; preparation of the CRF; opening of a toll-free telephone line; communication documents; preparation of the centralized randomization; construction of a study management database; database construction; database and document tests of observation; printing of the CRF.

Data collection: Collection sites: inclusion, visits; quality control, monitoring of the study (promoter)

Analysis and interpretation: data management; statistical analysis, writing an analysis report, interpretation.

Resource requirements

Staff members

Epidemiologist: 6 months preparation (0.2 full-time equivalent) - project follow-up 12 months (0.1) – 3 month analysis interpretation (0.2)

Project manager: 6 months of preparation (0.5) - 9 months project follow-up (0.2) – 6 month study report, communication to patients (0.5)

Secretary: 21 months (0.2 x 6 months + 0.2 x 3 months)

Clinical research asssociate: patient management and data collection: 3 months preparation specification documents (0.3) - 3 months preparation recruitment (0.3) - 9 months monitoring and collection of data (0.5)

Data entry technician: 9 months (0.1)

Database and statistics engineer: 3 months construction (0.2) - 9 months data management (0.1) - 3 months statistical analysis and statistical report (0.3)

Functioning

Printing of CRF

Laptop computer

Small supplies

Travel in urban areas

Estimated budget

| Ressources | Year 2011 | Year 2012 | Year 2013 | Total |
| --- | --- | --- | --- | --- |
| *Sponsoring* |  |  |  |  |
| Insurance | 800 |  |  | 800 |
|  |  |  |  |  |
| Ethics, regulatory submissions | 800 |  |  | 800 |
| (subtotal 1) | *1600* |  |  | *1600* |
|  |  |  |  |  |
| Staff members |  |  |  |  |
| Epidémiologist | 5000 | 5000 | 2500 | 12500 |
| Project manager | 5000 | 11000 | 10000 | 26000 |
| Clinical research associate 0.75 full-time equivalent | 3500 | 31500 |  | 35000 |
| Nurse of research clinical (follow-up 6 weeks, 3 and 6 months) of 300 patients 1 full-time equivalent |  | 50000 |  | 50000 |
| Input technician | 0 | 3000 | 0 | 3000 |
| Secretary | 1800 | 1800 | 1800 | 5400 |
| Engineer based in data - biostatistician | 2250 | 3400 | 3300 | 8950 |
| (subtotal 2) | *17550* | *105700* | *17600* | *140850* |
|  |  |  |  |  |
| *Functioning* |  |  |  |  |
| Printing | 5000 |  |  | 5000 |
| Laptop computer | 1200 |  |  | 1200 |
| Travel, phone | 500 | 2000 | 500 | 3000 |
| Small equipment | 500 | 200 | 500 | 1200 |
| (subtotal 3) | *7200* | *2200* | *1000* | *10400* |
| (subtotal 1+2+3) | *26350* | *107900* | *18600* | *152850* |
|  |  |  |  |  |
| Financial expenses |  |  |  |  |
| Structure costs  CIC-EC (10%) | 2635 | 10790 | 1860 | 15285 |
| Promoter Fees (management, monitoring) (10%) | 2898,5 | 11869 | 2046 | 16813,5 |
| (subtotal 4) | *5533,5* | *22659* | *3906* | *32098,5* |
| Total (1+2+3+4) | 31883,5 | 130559 | 22506 | 184948,5 |

Patients will be compensated for their transport according to a fixed price.

Physiotherapy school and physical medicine department and Rehabilitation

Physiotherapist trainees (completion of phase 2 of the active spa therapy) do not receive a remuneration over the academic period; they will in fact be partially assigned to the study from their internship field. However, during school holidays, physiotherapist trainees will receive remuneration according to the rates in force, i.e,. the gross monthly minimum wage of 1365€; for 8 part-time physiotherapist students for 2 months, the cost total is 10 920€.

They will be supervised by a physiotherapist from the Training Institute in Masso-Kinesitherapy (hourly cost = 44.37€ in charge of social taxes).

Over 6 weeks, 4 groups of 8 patients will be treated at a rate of 9 afternoons of 5 hours. Either 90 hours per cycle or a total cost for the 5 cycles of 450 hours x 44.37 = 20,000 euros

Reception and maintenance staff

These agents are part of Nancy Thermal's staff

